### Statistical Methods

Descriptive statistics for demographic data and outcome variables will be presented by using means and SDs for continuous variables that are normally distributed, medians and IQRs for continuous variables that are not normally distributed, and frequency tables for the categorical variables of each study arm and the whole sample. Baseline measures will be compared to assess balance between the two arms, using Fisher exact tests for categorical variables and Kruskal-Wallis tests for continuous variables. With regard to our analytic approach for missing data.

### Acceptability of the PLR and Vaginal Insert

For the PLR and vaginal insert, an overall acceptability index will be calculated by summing the acceptability questionnaire item responses and dividing the sum by the total possible score. The index will be characterized by using means and SDs, and individual items will be reported by using medians and IQRs. For the PLR, results that are stratified by participant type (patient or partner) will be reported.

### Effectiveness of Using a PLR to Reduce Deep Dyspareunia

For the experimental and waitlist control arms, the difference in deep dyspareunia scores from week 4 to week 10 between the two arms will be assessed by using an analysis of covariance (ANCOVA)–based approach [27]. We will compare mean scores from weeks 5 to 10 between the two arms, using preintervention (weeks 1-4) mean scores as covariates in the model. Similar ANCOVA modeling will be used for the Female Sexual Distress Scale-Revised, Female Sexual Function Index, Generalized Anxiety Disorder-7, and Patient Health Questionnaire-9 scores. If the assumptions of the ANCOVA model are not met by the data set, then we will consider conducting other appropriate statistical analyses, such as the ANOVA-based approach, 2-tailed *t* tests, linear regression modeling, and nonparametric approaches for the ANCOVA model.

### Validity and Reliability of the Vaginal Insert for the Self-assessment of Deep Dyspareunia

Tenderness at each pelvic anatomic site, as assessed via the vaginal insert test, as well as the highest score across all anatomic locations, will be correlated with the mean deep dyspareunia score, highest deep dyspareunia score, and lowest deep dyspareunia score. The self-assessed tenderness scores will be correlated with self-reported deep dyspareunia scores, using the Spearman rank correlation test. Participants without sexual events during weeks 1 to 4 will be compared to participants with ≥1 sexual event.

The results of assessments of tenderness (“yes” or “no”) from the most recently performed clinical pelvic examinations, if applicable (these data are collected in EPPIC), will be correlated with self-assessed tenderness, as measured with the vaginal insert (score: range 0-10), by using a 2-tailed *t* test or Mann-Whitney *U* test.

To evaluate test-retest reliability, self-assessed tenderness scores for each anatomic site from the first assessment will be correlated with self-assessed tenderness scores from the second assessment to determine if the two sets of vaginal insert data are reproducible over time. This will be done by using scores (0-10) to calculate the intraclass correlation coefficient, as well as by categorizing tenderness (“yes” or “no”) and using the McNemar test.

With regard to our analytic approach for missing data, if the maximum amount of missingness in any variable is <5%, we will exclude cases with missing data via pairwise exclusion. Otherwise, if the maximum amount of missingness is >5%, multiple imputation via chained equations will be used to impute the missing values. Results from imputed data sets will be pooled to provide final results.

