**Methods:**

Ours is an investigator-initiated, 2-arm RCT. We will recruit 40 patient participants with diagnosed endometriosis between the ages of 19 and 49 years, as well as their sexual partners. The participating couples will be randomized in a 1:1 ratio into the experimental arm or the waitlist control arm. The length of the study period will be 10 weeks, during which time all participants will record deep dyspareunia severity following each episode of sexual intercourse. In weeks 1 to 4, all patient participants will record deep dyspareunia severity at each sexual encounter. In weeks 5 to 10, participants in the experimental arm will use the buffer during vaginal penetration; participants in the waitlist control arm will continue engaging in vaginal penetration as usual. Participants will complete questionnaires for assessing measures of anxiety, depression, and sexual function at baseline, at 4 weeks, and at 10 weeks. In the substudy, patient participants will self-assess dyspareunia by using a vaginal insert on 2 occasions, at least 1 week apart. The primary outcomes—the acceptability and feasibility of the buffer—will be assessed with descriptive statistics, and the secondary outcome—phallus length reducer effectiveness—will be assessed by using an analysis of covariance–based approach. For the vaginal insert, we will assess acceptability, test-retest reliability, and convergent validity via correlation analyses comparing the use of the insert to clinical examination in terms of dyspareunia assessment outcomes.

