### Eligibility Criteria

Eligible patient participants will be new or rereferred patients in EPPIC who attended a clinic visit between January 1, 2018, and December 31, 2020; those who consented to being contacted for future research; and those who have a history of surgically confirmed endometriosis. Details of the inclusion and exclusion criteria are listed in Textbox 1.

Inclusion and exclusion criteria for the patient participants and their partners.

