#### Substudy Outcomes

The substudy will explore the acceptability and the preliminary convergent validity and test-retest reliability of a vaginal insert for the self-assessment of deep dyspareunia. The vaginal insert acceptability substudy outcome is based on an 18-item, built-for-purpose questionnaire adapted from a previously published measure for assessing the acceptability of female condoms [21] on a response scale ranging from 1 to 5. This questionnaire will be completed by all patient participants by week 4 (Multimedia Appendix 1).

Participants will use the vaginal insert to palpate various pelvic organs and structures (ie, to palpate the bladder anteriorly, the pelvic floor laterally, the pouch of Douglas posteriorly, and the cervix at the apex of the vagina) that have been previously associated with deep dyspareunia [26], and they will indicate whether they feel pain (“yes” or “no”) and the severity of the pain (11-point numeric rating scale wherein 0 corresponds to no pain and 10 corresponds to the worst pain). The number of tender sites for each participant will be calculated based on the self-reported number of tender anatomic sites that the participants identify when using the insert. Data on clinically assessed tenderness (“yes” or “no”) for each participant were previously collected through digital pain mapping, which was completed by a clinician. Data for clinically assessed tenderness are stored in EPPIC. These pain-related variables will be used to assess the convergent validity and test-retest reliability of the vaginal insert.

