## Results

The results from our study are expected to be submitted for publication by the spring of 2023. As of September 2021, we have recruited 31 couples into the study.

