The strengths of the protocol include having a randomized design, taking prospective pain measurements at each sexual encounter, and supplementing the trial by embedding the vaginal insert as a potential novel self-assessment tool. One limitation of the protocol is that it is not placebo controlled; however, it would be difficult to design a placebo for the PLR. Another limitation is that we will be comparing the vaginal insert to clinical examinations that are done at entry into the registry, which may be conducted several months before enrollment into the trial. In a future study, a pelvic examination can also be performed at recruitment. Furthermore, a limitation of the pilot trial is that we will not control for variables like age and BMI, which are potential confounders that may affect the use of the vaginal insert or PLR.

In summary, the PLR may be a noninvasive self-management tool for people with endometriosis-associated deep dyspareunia. The results of our pilot RCT will inform a future full-scale RCT of both the PLR and the vaginal insert test. The results from our study will be reported in peer-reviewed journals, in conference presentations, and to the study participants and the public through plain-language knowledge translation strategies. Ultimately, these innovations will contribute to the body of work on the rigorous investigation and evidence-based management of endometriosis-associated deep dyspareunia.

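### For the insert against clinical examination, the plan promises correlation but names only a two-group test, with no estimate of strength or agreement, and describes the reference examination inconsistently

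*Protocol article*

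**What the plan says.** The abstract (Methods) promises "convergent validity via correlation analyses comparing the use of the insert to clinical examination in terms of dyspareunia assessment outcomes". The section on validity and reliability of the vaginal insert gives the method: yes/no tenderness from the latest pelvic examination, where there is one, "will be correlated with self-assessed tenderness, as measured with the vaginal insert (score: range 0-10), by using a 2-tailed" t test or a Mann-Whitney U test. No coefficient, AUC or agreement measure is named for this comparison. The same section does name estimates for its other questions: insert scores are compared with self-reported dyspareunia "using the Spearman rank correlation test", and test-retest uses the intraclass correlation coefficient on the scores, plus the McNemar test on the yes/no data.

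Under Substudy Outcomes, women record pain at each structure both as yes or no and as a 0-10 score. The clinician's yes/no data "were previously collected through digital pain mapping, which was completed by a clinician".

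On the reference examination, the statistical section takes the latest one. The Discussion instead describes examinations made on entry to the registry, "which may be conducted several months before enrollment into the trial". Eligibility Criteria admits new or rereferred patients who "attended a clinic visit between January 1, 2018, and December 31, 2020". The Results section states: "As of September 2021, we have recruited 31 couples into the study". The target under Sample Size is 40 couples.

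**The concern.** A validation substudy has to show how closely the new tool tracks the existing assessment. A p value from a two-group comparison shows only whether the data are compatible with no difference between tender and non-tender women. With about 40 women, a just-significant result could be taken as support for the insert even if it discriminates poorly, and a non-significant one could be taken as failure even if the interval still includes useful discrimination.

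The age of the reference adds to this. If some examinations are old, weak association may reflect an outdated comparator and not a poor insert. A reader can judge that only if the plan says which examination is used and the report gives the intervals. The Discussion says the results will inform a full-scale trial of the insert test as well as of the buffer, so the size of the association is what the next study needs.

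**Working it through.** The article gives no precision or power figure for this comparison, so there is none to reproduce. Three checks were made.

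**1. What the named tests can and cannot give.** For a binary variable and a score, with n = n1 + n0:
- the equal-variance t statistic gives the point-biserial correlation, r = t / √(t² + n − 2), with the same p value;
- the Mann-Whitney statistic gives AUC = U / (n1·n0), and rank-biserial correlation = 2·AUC − 1.

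On three simulated sets of 0-10 scores:

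| Split | p, t test | p, point-biserial | r | AUC | Rank-biserial |
|---|---|---|---|---|---|
| 20/20 | 0.0447 | 0.0447 | 0.319 | 0.69 | 0.385 |
| 12/28 | 0.0840 | 0.0840 | 0.277 | 0.66 | 0.318 |
| 30/10 | 0.0350 | 0.0350 | 0.334 | 0.74 | 0.473 |

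So the tests do address association. What is missing is the estimate and its interval, and both come from the same statistics.

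**2. How much a p value hides at this size.** Assumed: 40 women, all with an examination, 12 tender and 28 not, observed AUC 0.70, two-sided 5% level. The article gives no split.
- Hanley-McNeil: Q1 = 0.70/1.30 = 0.5385; Q2 = 2(0.49)/1.70 = 0.5765.
- Variance = [0.70·0.30 + 11(0.5385 − 0.49) + 27(0.5765 − 0.49)] / (12·28) = 3.078/336 = 0.00916, so SE = 0.096.
- 95% CI = 0.70 ± 1.96·0.096 = 0.51 to 0.89. On the rank-biserial scale the estimate is 0.40, CI about 0.02 to 0.78.
- Mann-Whitney: z = 0.20 / √(41/(12·12·28)) = 0.20/0.1008 = 1.98, p = 0.047.

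By the correlation route (t critical value, Fisher z interval):

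| n (assumed) | Smallest significant r | Its 95% CI | 95% CI if r = 0.50 |
|---|---|---|---|
| 40 | 0.31 | 0.00 to 0.57 | 0.22 to 0.70 |
| 24 | 0.40 | 0.00 to 0.69 | 0.12 to 0.75 |

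The smaller n is shown because the comparison is made only where an examination exists.

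**3. How old the examination may be.** Inputs are the visit window in Eligibility Criteria and the recruitment date in Results.
- 1 January 2018 to 1 September 2021: 1,339 days / 30.4375 = 44.0 months.
- 31 December 2020 to 1 September 2021: 244 days / 30.4375 = 8.0 months.
- Counting to 30 September 2021 instead gives 44.9 and 9.0 months.

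By then 31 couples were in and 40 − 31 = 9 were still to come; for those, both limits only grow. These are the limits that the dates permit. The start of enrolment and the examination dates are not given, and a later examination may be on file.

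**The case against.** The strongest reply is that the chosen tests are sound. A reader might infer from the word correlated that a t test or Mann-Whitney test measures no association. That is wrong: the first check shows that the equal-variance t test is the test of the point-biserial correlation and that U is a rescaled AUC. Comparing scores between tender and non-tender women is an accepted known-groups approach. This stands, and the planned tests can stay.

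It can also be said that effect sizes are reporting detail for a fuller plan, and that preliminary convergent validity does not require agreement statistics. The second part has some force, and kappa is an addition more than a correction. The first has less: this section does name coefficients for its other comparisons, and here it settles on a test alone.

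The 12/28 split and the AUC of 0.70 are assumed, and any barely significant result has an interval reaching almost to the null. An AUC would be just as imprecise. True, but the interval would make that imprecision visible.

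On the examination's age, the authors already disclose a gap and suggest an examination at recruitment in a future study. A reader might infer from the dates that examinations were in fact years old; the article does not establish that. Nor does the Recruitment section say that treatment came between examination and enrolment. It explains the dyspareunia threshold of 4 or more as a way to exclude women whose symptoms had been reduced by surgery or other interventions, and gives no timing.

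**Conclusion.** The point holds in a limited form. The abstract and the statistical section promise correlation with clinical examination, while the method named would give a p value without any measure of strength or agreement. Under the assumptions shown, a significant result at n = 40 is compatible with an AUC from 0.51 to 0.89, or with a correlation from near zero to 0.57.

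The two accounts of the reference examination conflict. Because rereferred patients are eligible, the latest examination and the one at registry entry need not be the same. The stated gap of several months understates what the article's own dates allow: about 8 to 44 months for a couple enrolled in September 2021, unless a later examination exists. That is a possibility, not a finding about the women enrolled.

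The primary outcomes and the sample size are untouched. This is a worthwhile clarification of one comparison in an exploratory substudy.

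**What to change.** - For each site with clinician data, report the AUC (or the rank-biserial or point-biserial correlation) of the 0-10 insert score against clinician yes/no, with a 95% CI. Site-level clinician data are implied by the pain mapping but not stated outright, so confirm that they exist.
- For yes/no against yes/no, report kappa with a 95% CI, and sensitivity and specificity with CIs as description. Both variables are already recorded.
- Keep the t test or Mann-Whitney test if wanted, and describe it as a comparison of groups.
- State one rule for which examination is used and make the statistical section and the Discussion agree.
- Report the distribution of the examination-to-enrolment interval and restate the limitation with the actual range.
- Keep all women in the main analysis and show those with recent examinations only as a sensitivity analysis. A cut-off such as 12 months has no basis in the article. For a couple enrolled on 1 September 2021 it would admit only visits in the last 4 of the 36 window months (4/36 = 11% if visits were evenly spread, an assumption), unless a later examination is on file.

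The cost is wording, a little more analysis, and examination dates, which should be obtainable from the team's own registry. No sample size changes. The intervals will be wide with about 40 women and should be presented as such.

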### Sample Size

A sample size for a pilot study is often recommended to be at least 12 per group [19]. Given potential dropout and the uncertainty around the variance in acceptability, we will aim to recruit 20 participants and their sexual partners per group (ie, 40 couples or 80 total study participants).

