### Assignment of Interventions

The study coordinator will use a REDCap (Research Electronic Data Capture; Vanderbilt University) extension package called *randomization* to randomly assign consented participants in a 1:1 ratio to 1 of 2 study arms; the experimental PLR arm will receive the PLR, and the waitlist control arm will receive the PLR once the study has concluded. Both arms will receive the vaginal insert for the substudy.

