### Participant Timeline

Throughout the study, all participants will continue concurrent endometriosis treatments and treatments for other conditions as usual. At the start of the study, both arms will complete baseline demographic, psychological, and sexual function questionnaires. In weeks 1 to 4 of the study, patient participants in both arms will engage in sexual activity as usual and be asked to record a daily diary of all sexual events and the severity of deep dyspareunia (score: range 0-10). Psychological and sexual function questionnaires will be repeated at the end of week 4. In week 5, participants in the experimental arm will receive and begin to use the PLR. Participants in the waitlist control arm will not receive the PLR and will continue to record deep dyspareunia severity at each sexual encounter. At the end of week 10, all patient participants will repeat the psychological and sexual function questionnaires, and participants in the experimental arm will indicate the acceptability of the PLR. At the conclusion of the study period, participants in the waitlist control arm will receive the PLR.

For the substudy, during weeks 1 to 4, all patient participants will self-assess deep dyspareunia by using the vaginal insert on weeks 2 and 3 of their menstrual cycle or on another two occasions (1 week apart) in the absence of regular bleeding. At the end of week 4, all patient participants will indicate the acceptability of the vaginal insert. The participant timeline is depicted in Table 1.

**Table 1 table1:** Schedule of interventions and assessments.

Groups and activities					Weeks 1 to 4							Weeks 5 to 10		
					Start of study		Vaginal insert self-assessment		Midstudy questionnaire		Experimental period			End of study

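### The yes/no part of the vaginal insert's test-retest analysis rests on the McNemar test alone, which detects a shift between sessions but does not measure within-person agreement

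*Protocol article*

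**What the plan says.** The section of the protocol article on validity and reliability of the vaginal insert states the aim of the repeat assessment as "to determine if the two sets of vaginal insert data are reproducible over time". It names two methods, applied site by site. For the severity ratings: "This will be done by using scores (0-10) to calculate the intraclass correlation coefficient". For the binary data, the plan is to class tenderness as yes or no "and using the McNemar test". No agreement statistic is named for the binary data, and no significance level or threshold is given for calling the insert reliable.

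Under Substudy Outcomes, the sites are the bladder, pelvic floor, pouch of Douglas and cervix, and at each one the patient records both a yes/no answer and a 0-10 severity. Participant Timeline has each patient use the insert twice in weeks 1 to 4, one week apart. Under Assignment of Interventions, "Both arms will receive the vaginal insert for the substudy", so all 40 planned patients (20 per arm, Sample Size) would contribute a pair of readings per site.

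**The concern.** The question is whether a patient who reports a site as tender at the first session reports it as tender at the second. That is a question about agreement within a person, and the answer lies mainly in how many patients give the same answer twice. McNemar discards those patients. It compares only the yes-to-no changes with the no-to-yes changes, and so tests whether the overall proportion tender is the same at both sessions.

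Test-retest reliability is a stated aim of the substudy, the Discussion gives reproducibility as the reason for the second use of the insert, and the results are meant to inform a later full-scale trial that includes the insert test. If the binary result is reported as planned, a reader is invited to take a non-significant p-value as support for reproducibility. It would carry no such information.

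**Working it through.** **Inputs.** The document gives no figure for this analysis, so there is nothing to reproduce first. From the document: two readings per patient per site, and n = 20 + 20 = 40 patients planned. For sensitivity, n = 31 (couples recruited by September 2021, Results) and n = 24 (the 12 per group cited under Sample Size, times 2). Assumed, because not in the document: two-sided alpha of 0.05 and a proportion tender between 0.3 and 0.7.

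**Notation.** Per site, a = yes/yes, b = yes/no, c = no/yes, d = no/no.

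- Observed agreement: Po = (a + d)/n.
- Chance agreement: Pe = [(a + b)/n][(a + c)/n] + [(c + d)/n][(b + d)/n].
- Cohen's kappa = (Po − Pe)/(1 − Pe).
- Exact McNemar p: two-sided binomial test of b out of b + c against 0.5. Neither a nor d enters.

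**Step 1: no agreement beyond chance.** Take a/b/c/d = 10/10/10/10.

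- Po = 20/40 = 0.50.
- Pe = 0.5 × 0.5 + 0.5 × 0.5 = 0.50.
- kappa = 0.
- b = c = 10, so p = 1.0.

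**Step 2: good agreement with a one-way shift.** Take 20/6/0/14.

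- Po = 34/40 = 0.85.
- Proportion tender: 26/40 = 0.65 at session 1 and 20/40 = 0.50 at session 2.
- Pe = 0.65 × 0.50 + 0.35 × 0.50 = 0.50.
- kappa = (0.85 − 0.50)/0.50 = 0.70.
- Exact p = 2 × (1/2)^6 = 0.031. The chi-square version gives 0.014, and 0.041 with continuity correction.

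On agreement, the second table is clearly better than the first. The McNemar p-values do not rank them that way, because they answer a different question.

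**Step 3: how often no repeatability gives a non-significant result.** Suppose the two answers are independent with the same proportion tender, so true kappa is 0. Each kind of change then has probability p(1 − p). Enumerating all discordant counts gives the probability of a non-significant McNemar test, over p = 0.3 to 0.7:

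| n | exact | chi-square | continuity-corrected |
|---|---|---|---|
| 40 | 0.970-0.971 | 0.947-0.950 | 0.973-0.976 |
| 31 | 0.972-0.975 | 0.952-0.956 | 0.976 |
| 24 | 0.976-0.977 | 0.957-0.958 | 0.977-0.978 |

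This is as expected. With equal proportions the null hypothesis of McNemar is true, so the exact test is non-significant at least 95% of the time whatever the kappa. A highly repeatable insert and one with no repeatability both give that result.

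**Step 4: sensitivity of the significant case.** With 5 one-way changes out of 40 (18/5/0/17: 87.5% agreement, kappa 0.75), p is 0.063 exact, 0.025 chi-square and 0.074 corrected. Whether a small shift reaches 0.05 therefore depends on which variant is used; step 2 does not.

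**The case against.** Four points can be made for the plan.

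- **The ICC is planned as well.** It uses the 0-10 scores from the same patients, sites and sessions, and it is a proper repeatability measure. A reader might infer from the McNemar problem that an insert with no repeatability could pass the reliability assessment as a whole. The document does not support that: an unrepeatable insert would be expected to show a low ICC. This point stands, and it confines the problem to the yes/no classification.
- **There is no pass/fail rule.** The protocol nowhere says that a non-significant McNemar result means reliable. That also stands. The weakness is that the test is assigned to reproducibility, which invites the inference, and that no other statistic is named for the binary data.
- **A shift is part of reproducibility.** A reader might infer that McNemar would wrongly condemn a repeatable insert. In the 20/6/0/14 table, however, the proportion tender really falls from 65% to 50%, and every change goes the same way. Flagging that is a true detection. The two sessions are planned for different weeks of the menstrual cycle where there is regular bleeding, so a check for shift has a place. McNemar is incomplete here, not useless.
- **An unseen analysis plan may add kappa.** It may. But the point is not that detail is missing: the article names a specific test for a specific purpose, and that test does not serve it.

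**Conclusion.** The point holds for the yes/no component. The only method named for it cannot show within-person agreement. At n = 40, answers unrelated between sessions but with equal proportions tender give a non-significant result with probability about 0.95 to 0.98, depending on the test variant. A significant result shows a directional shift and can occur with 85% agreement and kappa 0.70.

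The mismatch between test and question follows from the definition of McNemar and needs no assumed figure. The probabilities rest on the assumed alpha of 0.05, the assumed range for the proportion tender, and complete pairs.

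The reach is limited. This is one of two reliability analyses in an exploratory substudy, the other is sound, and the data remain usable. The primary outcomes (device acceptability and study feasibility) and the secondary effectiveness outcomes do not draw on it. It is a minor to moderate methods correction.

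**What to change.** In the validity and reliability section, change the sentence on the binary data so that, for yes/no tenderness at each site:

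- the reliability measure is percent agreement (overall, positive and negative) and Cohen's kappa, each with a 95% confidence interval, with the prevalence-adjusted bias-adjusted kappa (PABAK) alongside where nearly all or nearly no patients are tender;
- McNemar is kept, if wanted, only as a check for systematic shift between sessions, described as such and not read as evidence for or against agreement.

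Keep the ICC for the 0-10 scores.

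The cost is about one sentence of wording. The same 2x2 counts that McNemar needs supply every statistic above, so data collection and sample size do not change.

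### One variable above 5% missing sends insert retests never done, and dyspareunia scores that are undefined, into imputation; the insert's reliability and validity should rest mainly on observed pairs

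*Protocol article*

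**What the plan says.** The rule closes the section of the protocol article on the validity and reliability of the vaginal insert. Its lower branch is "if the maximum amount of missingness in any variable is <5%, we will exclude cases with missing data via pairwise exclusion". Its upper branch is "if the maximum amount of missingness is >5%, multiple imputation via chained equations will be used to impute the missing values", followed by "Results from imputed data sets will be pooled to provide final results". No variable or analysis is exempted.

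The same section sets out the analyses concerned:

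- **Test-retest reliability at each site.** "This will be done by using scores (0-10) to calculate the intraclass correlation coefficient", with a McNemar test on the yes/no version.
- **Convergent validity against the diary.** Spearman correlations of insert scores with the mean, highest and lowest deep dyspareunia scores.
- **Convergent validity against the clinic.** Insert scores compared with tenderness "from the most recently performed clinical pelvic examinations, if applicable".

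The section also expects some women to have no sexual event in weeks 1 to 4 and plans to compare them with the rest. Eligibility Criteria (Textbox 1) admits women who are not sexually active because of deep dyspareunia and asks only for willingness to have penetrative sex once during the study.

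On numbers, Sample Size says "we will aim to recruit 20 participants and their sexual partners per group (ie, 40 couples or 80 total study participants", and Results says "As of September 2021, we have recruited 31 couples into the study".

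**The concern.** One switch serves variables of very different kinds. It looks at the worst variable and then fills every gap, without separating a value that exists but was not recorded from a value that was never generated.

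Two cases matter. A woman who skips the second insert session provides no information on her own repeatability. If her retest is imputed, her contribution to the ICC comes from the imputation model. A woman with no sexual event in weeks 1 to 4 has no mean, highest or lowest dyspareunia score for that period. Imputing one and correlating it with her insert readings tests convergent validity against a number that stands for nothing.

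At stake are the substudy's estimates of repeatability and convergent validity, which the Discussion says will inform a full-scale trial of the insert test as well as of the device.

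**Working it through.** The article gives no target ICC, expected missingness or imputation model, so there is no stated figure to reproduce.

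**1. When the switch trips.** Missing share = m/N.
- N = 40 (planned): 2/40 = 5.0%; 3/40 = 7.5%. Three missing values in one variable start imputation.
- N = 31 (recruited by September 2021): 1/31 = 3.2%; 2/31 = 6.5%. Two do.

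**2. How easily it trips.** Assume each value is missing with probability q. For one variable p = P(X ≥ r), with X binomial(N, q), r = 3 at N = 40 and r = 2 at N = 31. For k independent variables the chance is 1 − (1 − p)^k. Four sites by two sessions give k = 8. A skipped session removes four scores together, so independence overstates the chance; k = 2 treats each session as one unit.

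| N | q | p | k = 8 | k = 2 |
|---|---|---|---|---|
| 40 | 2% | 0.046 | 0.312 | 1 − 0.954² = 0.09 |
| 40 | 5% | 0.323 | 0.956 | 1 − 0.677² = 0.54 |
| 31 | 2% | 0.127 | 0.663 | 1 − 0.873² = 0.24 |
| 31 | 5% | 0.463 | 0.993 | 1 − 0.537² = 0.71 |

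The diary score can trip the switch alone: three women of 40, or two of 31, with no event in weeks 1 to 4 are enough.

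**3. Effect on the ICC.** All inputs are assumptions: four sites, two sessions, scores rounded to 0–10, latent ICC 0.8 (about 0.77 to 0.78 after rounding), 10 imputations, 300 replicates (150 at N = 31 and N = 400). The statistic is ICC(2,1) at one site. Unless stated, N = 40, 20% of second sessions are missing by chance, and imputation uses a normal model.

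| Imputation model | Full data | Observed pairs | Imputed | Imputed − observed |
|---|---|---|---|---|
| Same-site reading, 10% missing | 0.783 | 0.782 | 0.781 | −0.001 |
| Same-site reading | 0.777 | 0.775 | 0.769 | −0.006 |
| Same-site reading, predictive mean matching | 0.778 | 0.777 | 0.763 | −0.014 |
| All 8 insert variables | 0.772 | 0.771 | 0.747 | −0.024 |
| All 8, N = 31 | 0.778 | 0.778 | 0.742 | −0.036 |
| All 8 plus 8 irrelevant variables | 0.771 | 0.768 | 0.702 | −0.066 |
| Insert readings left out, 10% missing | 0.768 | 0.768 | 0.687 | −0.081 |
| Insert readings left out | 0.772 | 0.771 | 0.596 | −0.175 |
| All 8, N = 400 | 0.778 | 0.779 | 0.777 | −0.002 |
| High first-session pain causes skipping, same-site reading | 0.777 | 0.751 | 0.763 | +0.012 |
| High first-session pain causes skipping, all 8 | 0.779 | 0.754 | 0.749 | −0.005 |

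A second simulation used predictive mean matching, N = 40, an assumed ICC of about 0.68 and 10–20% of retests missing. Imputation gave a lower ICC than observed pairs in all 16 scenarios, including those with pain-related skipping. The gap was about 0.01–0.02 with a same-site model and about 0.09–0.11 with 16 auxiliary variables at 20% missing.

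For scale, the observed-pairs ICC varied between replicates with a standard deviation of about 0.07 to 0.08 at N = 40 and 20% missing. A small model costs little against that; an overloaded one costs about one standard deviation.

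**The case against.** The strongest reply is that the article names chained equations but no imputation model, and that an article may leave the model to a fuller plan. A reader might infer that the rule itself biases the insert's reliability downward. The documents do not support that. With the paired reading in a small model the ICC hardly moves. In one scenario, where high first-session pain causes skipping, imputation (0.763) came nearer the full-data value (0.777) than observed pairs did (0.751). This stands: a fall is a risk that depends on the model, not a consequence of the rule.

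Four other strong readings also go too far.

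- **Non-existent examinations will be filled in.** Substudy Outcomes says clinical tenderness was already collected on every participant, and the qualifier in the validity section may simply limit the comparison to women who have an examination. The two statements need reconciling; neither shows that imputation is intended.
- **The whole trial moves to imputation.** The paragraph sits in the insert section, and the general Statistical Methods section, in the text at hand, breaks off at the same opening words. The scope is unclear.
- **Exactly 5% is left uncovered.** This arises only at 2 of 40, and the upper branch opens with a word that implies it takes everything else. It is a matter of tidying.
- **The rank and McNemar tests cannot be pooled.** Test statistics can be combined across imputations, and McNemar corresponds to a paired difference in proportions. The objection is minor.

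What the reply does not remove is the written rule. The trigger, the absence of exemptions and the final status of pooled results are all stated, so this is not an omission that a fuller plan would fill.

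**Conclusion.** The point holds in a limited form. As written, one variable above 5% missing leads to imputation of all missing values as the final result, including retests never done and weeks 1 to 4 dyspareunia scores that are undefined. At N = 31 to 40 this makes the insert's ICC and correlations depend partly on an unstated model. The ICC can be lowered, from a negligible amount with a small model that contains the paired reading to about 0.1 with an overloaded one; leaving the insert readings out of the model costs more still. These sizes rest on assumed ICCs, missing rates and models.

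The undefined diary scores are the firmer example, because the plan itself expects women without events. The point is minor to moderate: the substudy is exploratory and no ICC threshold or decision is attached to it.

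**What to change.** Reword the missing-data paragraph in the insert validity and reliability section:

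1. Make observed pairs, with n stated for each analysis, the main analysis of test-retest reliability and convergent validity. Report multiple imputation as a sensitivity analysis only.
2. Do not impute values that do not exist (no sexual event in weeks 1 to 4, no insert session, no examination where none applies), and do not count them towards the threshold. Reconcile the qualifier on clinical examinations with the statement in Substudy Outcomes that these data were collected on every participant.
3. Decide imputation separately for each ANCOVA, from the variables in that model and with a short predictor list. Cover the diary-based deep dyspareunia ANCOVA as well as the questionnaire ones. Its covariate is the weeks 1 to 4 mean, so state how a woman with no event in those weeks is handled.
4. Write the upper branch as 5% or more.

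The cost is a few lines of text, fewer women in some substudy analyses and slightly wider intervals there. Observed pairs can themselves be somewhat biased if skipping depends on pain; comparison with the sensitivity analysis would help to show this.
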